### Study design

This investigation is a 16-week, randomized, crossover, double-blinded, placebo-controlled exploratory study of the safety and tolerability of a nutritional formulation containing *d*, *l*-beta-hydroxybutyrate mineral salts (sodium, calcium, magnesium) (trumacro™, Disruptive Nutrition, LLC, Durham, NC, USA) for use with a KD, a LGIT diet, and standard diet in subjects with AS. It is being conducted in accordance with the Declaration of Helsinki and is approved by the Institutional Review Board (IRB) at Vanderbilt University Medical Center (protocol number [name]10212017084407). See Fig. 1 (Standard Protocol Items: Recommendations for Interventional Trials (SPIRIT) Figure: schedule of enrollment, interventions, and assessments), Additional file 1 for the SPIRIT 2013 Checklist (recommended items to address in a clinical trial protocol and related documents), and Additional file 2 for the schematic of the trial design.

**Fig. 1 Fig1:**
[figure not shown]
FANS trial design – randomized, placebo-controlled, crossover study. Standard Protocol Items: Recommendations for Interventional Trials (SPIRIT) Figure; schedule of enrollment, interventions, and assessments. *May be conducted by telephone or in person at the clinic site. **An additional sample of blood will be collected during the baseline visit and added to a repository. Samples may be used for studies such as DNA and RNA, proteomics, and metabolomics and may be used for ancillary studies unrelated to the current trial. At the time of publication, no other studies have been planned

Members of the Vanderbilt research team, including the lead investigator and clinical trial coordinators, are responsible for obtaining informed consent (see Additional file 3). Consent is primarily sought through remote interview prior to scheduling the baseline visit in order to reduce travel burden on patients and families. On the consent form, participants will be asked if they agree to the use of their data and banked blood samples should they choose to withdraw from the trial. Participants will also be asked for permission for the research team to share relevant data with people from the institution taking part in the study as well as regulatory agencies where required. After obtaining informed consent from the parent/caregiver, subjects enter a 2-week run-in period. At the beginning of the run-in period the natural history and medical history is collected from the subject’s parent/caregiver. At baseline, a 3-day recall record of the subject’s diet, appetite, GI health, sleep, seizure, mood, and activity level are collected. While one goal of this study is to assess the effects of dietary background on the suitability of the nutritional formulation, there is no requirement for a specific number of patients per diet due to the rarity of the population. Additional study measures, including physiologic, are also collected (Fig. 1).

The study design for this nutritional intervention protocol is a randomized, double-blind, placebo-controlled, crossover study. There are two arms to the study, (1) an investigational formulation period followed by a placebo formulation period, or (2) a placebo formulation period followed by investigational formulation period. Each patient will receive both the investigational formulation and the placebo formulation, with a washout period between each arm. The randomization schedule was created by the Investigational Drug Service Pharmacy using randomization software in a 1:1 ratio with a block size of 4. Participants are enrolled in the next open slot of on the randomization table. The nutritional formulations are coded by the manufacturer lot number and, therefore, the clinical staff is blind to the actual contents of the container (active verses placebo).

Once randomized, subjects start Intervention Period 1, a 4-week period in which they receive nutritional formulation containing BHB or placebo while maintaining the diet noted at entrance into the study. Home monitoring occurs as indicated in Fig. 1. After 4 weeks of blinded intervention, subjects are evaluated in the clinic and then cease consumption of the ketone formulation or placebo for 4-week washout period. Following completion of the washout, subjects enter a second 4-week period in which they receive formulation versus placebo. They will continue the home monitoring throughout the duration of the study. Subsequently, at the completion of the second intervention, they undergo the final scheduled study visit and laboratory sampling. A washout period follows Intervention Period 2, and at approximately week 16 of the study, a follow-up call is made to the family to review symptoms and ensure the patient is not experiencing adverse events during this period. The trial schedule of enrollment, interventions, and assessments is outlined in Fig. 1 (FANS trial schedule of procedures).

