Additional oversight and auditing of the trial is provided by [name], Chief Science Officer of Disruptive Nutrition, LLC with weekly conferences with members of the Vanderbilt research team. In-person meetings are planned quarterly, with data auditing semi-annually. A medical and research advisory committee has been established and consists of independent experts and key opinion leaders. The committee meets semi-annually. The Data Safety Monitoring Board is discussed in a separate section of this protocol under “Data Monitoring.”

Patients are recruited to the Nashville, Tennessee site at Vanderbilt University. Subjects with AS are recruited through the lead investigator’s practice, physician referrals, outreach through social media, and parent support groups such as the Foundation for Angelman Syndrome Therapeutics and the Angelman Syndrome Foundation. Subjects are enrolled with the following inclusion criteria: genetically confirmed diagnosis of Angelman syndrome; age 4–11 years; currently on a LGIT, KD (conventional 4:1 or 3:1, MCT, modified Atkins), or standard diet (regular diet) consistently for at least 3 months; willingness to consume the investigational formulation; and willingness to undergo protocol examinations at home and clinic visits. Subjects are excluded if they: require parenteral nutrition; have major hepatic or renal dysfunction; have a history of diabetes or have diabetes; are significantly underweight with a body mass index < 18.5; participate in other clinical intervention studies within 1 month prior to entry to the study; are unwilling to comply with the protocol requirements; or have contraindications for the use of ketogenic or low-carbohydrate diets which, in the opinion of the investigator, may influence a patient’s ability to participate in the study. Subjects are permitted to continue using all previously prescribed medications, provided the prescriptions have not changed in the 1 month prior to randomization. Parents/guardians of all eligible subjects must sign informed consent prior to study enrollment, following adequate explanation of the aims, methods, objectives, and potential hazards of the trial by the responsible investigator (see Additional file 3).

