No studies testing ketone supplementation in patients with AS exist. Therefore, sample-size estimation is based on measures of ketosis. It is assumed from murine pre-clinical investigations, non-AS clinical studies using MCT and/or BHB, and low-carbohydrate dietary interventions, that the minimal change of the secondary outcome, degree of ketosis, from the baseline to the end of the fourth week of the investigational formulation intervention period will be 100% change from baseline (baseline for standard diet is typically < 0.5mmol/L of d-BHB in blood, or < 5 mg/dL acetoacetate in urine). The acetoacetate test used is Ketostix (Bayer Corp. Diagnostics Division, Tarrytown, NY, USA) which exhibits a sensitivity of 78% and a specificity of 96% when compared to a serum standard of 14.4 ml/dL. Considering a 25% drop-out rate, an estimate of 25 subjects need to be screened to achieve 15 completers.

Descriptive statistics, such as mean and standard deviation, are used to describe continuous variables, and frequency for the categorical variables. Means are compared using a paired two-sample *t* test. Statistical significance for all tests is *p* < 0.05. Multiple comparisons can be made including: (1) each subject to serve as their own control, comparing investigational formulation to placebo formulation, as well as to baseline, (2) each dietary background group considered in aggregate, comparing investigational formulation to placebo formulation, as well as to baseline, and (3) all subjects considered in aggregate, comparing investigational formulation to placebo formulation, as well as to baseline.

Any patient who receives the study formulation for any amount of time will be included in the intent-to-treat population for study analyses. Missing data points in this population will be addressed in discussion of any published results. Data from protocol-compliant participants is the defined population for efficacy subset analyses; any participant who received both protocol-required formulations and all required clinical assessments is considered protocol compliant. Such an efficacy subset analysis will be the primary approach for determining whether the trial endpoints are met. Those patients who complete the baseline visit, but do not start Intervention Period 1 and are withdrawn from the study, will be used for natural history reportable data only but will not be included in analyses for determining whether the outcome measures of the trial have been met.

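### The protocol sets a goal about the effect of dietary background, but the only diet analysis it names is separate within-diet tests, which neither estimate nor test a difference between diets

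*Protocol article*

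**What the plan says.** The goal is in the Study design section, in the text after Fig. 1: "While one goal of this study is to assess the effects of dietary background on the suitability of the nutritional formulation". The same sentence goes on to say that "there is no requirement for a specific number of patients per diet due to the rarity of the population".

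The inclusion criteria admit three dietary backgrounds, one with several variants. A child must be "currently on a LGIT, KD (conventional 4:1 or 3:1, MCT, modified Atkins), or standard diet (regular diet) consistently for at least 3 months".

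Statistical considerations gives the analysis. "Means are compared using a paired two-sample" t test, and "Statistical significance for all tests is" p < 0.05. The list of contrasts begins "Multiple comparisons can be made including". Its second item is the only one that concerns diet: "each dietary background group considered in aggregate, comparing investigational formulation to placebo formulation, as well as to baseline". No contrast of one diet with another is named, and no rule says how the within-diet results become a statement about diet.

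On size, the same section gives "an estimate of 25 subjects need to be screened to achieve 15 completers". It states neither an SD nor a power.

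**The concern.** Whether dietary background matters is a question of effect modification: is the formulation-minus-placebo difference larger on one diet than on another? Comparison (2) answers something else, namely whether that difference is distinguishable from zero within one diet at a time. A set of such tests contains no estimate of the difference between diets. This is true at any sample size and any effect size.

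If the within-diet p values are the only diet results produced, the natural way to address the stated goal is to note which diets reached significance and which did not. In groups this small, that pattern depends heavily on how many children happened to enrol on each diet. A diet with one child cannot be tested at all. At stake is a conclusion about diet that reflects group size and chance.

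**Working it through.** **Inputs from the protocol.** Three diet groups; 15 completers; paired t test; p < 0.05 for every test; no fixed number per diet.

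**Inputs assumed.** Two-sided tests, since sidedness is not stated. Normally distributed within-subject differences. The split across diets. The standardised effect d, which is the mean formulation-minus-placebo difference divided by the SD of those differences. The protocol's assumed 100% change concerns ketosis and comes without an SD, so it does not fix d.

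**The plan's own figure.** The protocol gives no figure for the diet analysis. Its only size figure is 25 screened for 15 completers with 25% drop-out. Drop-out alone gives 15 / 0.75 = 20 to enrol, or 25 × 0.75 = 18.75 completers. The two agree only with a further 20% screening loss, which is not stated (25 × 0.80 × 0.75 = 15). That is a separate matter; 15 is used below.

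**Step 1: power within a diet.** For n children, power is the chance that a noncentral t variable with n − 1 degrees of freedom and noncentrality d√n exceeds the two-sided 5% critical value. With all 15 children, 80% power needs d = 0.78. At that d, power is 13% for n = 3, 27% for n = 5 and 41% for n = 7.

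**Step 2: chance that the tests disagree when the true effect is the same on every diet.** For three diets with powers p1, p2 and p3:

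P(disagree) = 1 − p1·p2·p3 − (1 − p1)(1 − p2)(1 − p3)

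For 5/5/5 at d = 0.78: 1 − 0.269³ − 0.731³ = 1 − 0.019 − 0.391 = 0.59.

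For 5/5/5 at d = 0: 1 − 0.05³ − 0.95³ = 1 − 0.0001 − 0.8574 = 0.14.

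| Common effect d | Power per diet, n = 5 | P(disagree), 5/5/5 | P(disagree), 9/4/2 | P(disagree), two diets 8/7 |
|---|---|---|---|---|
| 0 | 5% | 14% | 14% | 10% |
| 0.5 | 14% | 36% | 38% | 34% |
| 0.78 (80% power in all 15) | 27% | 59% | 65% | 50% |
| 1.0 | 40% | 72% | 82% | 46% |
| 1.2 | 53% | 75% | 90% | 33% |
| 1.5 | 71% | 62% | 92% | 13% |
| 2.0 | 91% | 25% | 87% | 1% |

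A 7/5/3 split gives 61% at d = 0.78. At d = 0.90 (90% power in all 15) the 5/5/5 figure is 67%. For 5/5/5 the chance exceeds one half only for d of about 0.67 to 1.65. Simulation with 100,000 runs agreed with the exact results.

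**Step 3: what a direct comparison does.** A one-way F test of diet on the within-subject differences (5/5/5, 40,000 simulated runs) had a false-positive rate of about 5% at common effects of 0, 0.8 and 1.5 SD. When one diet truly differs by 1 SD, its power is 28% (5/5/5) or 16% (9/4/2).

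The 95% CI half-width for a difference between two diets, with the SD pooled over three diets (12 degrees of freedom), is 2.179 × √(1/n1 + 1/n2) in SD units:

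- 5 vs 5: 2.179 × √0.4 = 1.38 SD
- 9 vs 2: 2.179 × √(1/9 + 1/2) = 1.70 SD

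**The case against.** The strongest reply is that the protocol never says it will compare significance across diets. The list of contrasts is open, the study is called exploratory, the article condenses a fuller document, and the analysis plan is not shown. Diet is not among the primary or secondary objectives, and the sentence stating the goal itself admits that numbers per diet are uncontrolled. All of this is correct and limits the weight of the point. It does not remove the mismatch: the article states a between-diet goal and names, for diet, a contrast that does not address it.

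Three stronger readings are tempting, and the documents do not support them.

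- **That the plan will usually produce a false diet difference.** This depends on d, which the protocol does not fix. For balanced groups a split is a minority outcome at small effects and at very large ones. With two diets of 8 and 7 it is at most about 50%. Suitability also relates most closely to the tolerability measures, where the difference from placebo may be near zero. The 5/5/5 figure is then 14%, still above the 5% of a direct test.
- **That the trial would report the formulation as working or tolerated on one diet and not on another.** No text says so. The misreading needs someone to compare p values across diets.
- **That the diet result is meant to guide use by diet.** The Discussion says only that the knowledge gained may guide further evaluations.

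It can also be said that a direct contrast will leave the question largely unanswered. With 15 completers that is so, but a wide interval shows it openly, and a pattern of p values hides it.

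**Conclusion.** The point holds in a limited form. The goal concerns a difference between diets, and the only diet analysis named does not estimate or test one. That part needs no assumption.

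How often the named tests would disagree with no true difference between diets does rest on assumptions: the split, a common standardised effect, two-sided 5% tests and normal differences. For three equal groups of five the chance runs from 14% at no effect to a peak near 75% around 1.2 SD, and back to 25% at 2 SD. Uneven splits keep it high over a wider range of effects. So "can often disagree" is justified, and "will usually" is not. The open list and the exploratory label make this a correction to settle before analysis; it does not invalidate the trial.

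**What to change.** For the diet goal, replace the within-diet significance tests in comparison (2) with a direct estimate and 95% CI of the between-diet difference in the within-subject formulation-minus-placebo effect. Show individual results by diet without p values. Label the diet analysis descriptive, and state that no diet difference will be inferred from significance on one diet and not on another. If diets are to be pooled, the trial team should fix and justify the pooling before unblinding; the protocol gives no ground for a particular grouping.

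The cost is a change of wording and one further estimate from data already being collected. The downside is imprecision: a half-width of about 1.4 to 1.7 SD between two diets can exclude only very large differences. That is the limit of 15 completers.

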### Procedures and interventions

Background information regarding the subject’s natural history is collected using a REDCap© survey (Copyright 2006–2013 Vanderbilt University. All rights reserved) [16]. Body weight and height are measured at each study visit. Serum laboratory analysis is conducted to establish a metabolic baseline: comprehensive metabolic panel, complete blood count, ketones (beta-hydroxybutyrate and acetoacetate), and lipid panel. EEG, ERP and gait analysis using the ProtoKinetics Zeno™ Walkway are performed at each study visit (Fig. 1). The utility of ERP and gait analysis to predict changes in patient function in an Angelman population has not been clearly established, but their appropriateness in similar populations has been detailed elsewhere [17, 18]. Questionnaires completed during the study include the Vineland™-3, Developmental Behavioral Checklist (Pearson Education, Inc.), which has been used previously in studies of patients with AS [19], and the Callier-Azusa Scale to assess areas of motor development, perceptual abilities, daily livingskills, language development, and socialization. Dietary intake, seizure frequency, sleep, and GI health are evaluated throughout the protocol through at-home monitoring. Data collected during home monitoring is recorded on tablet devices provided to the parents/caregivers upon enrollment, preloaded with necessary tracking applications. Families are provided an EarlySense® monitor with a written guidance for home sleep monitoring. External sleep monitors are important in an AS population as wearable devices are typically removed by the patient. The monitors have not been studied with patients with AS; however, their validity has been demonstrated in the general population [20]. Urinary ketones are measured by the patient’s caregivers throughout the protocol, using Ketostix which are a validated measure of urine acetoacetate [21, 22].

Tolerability is determined at the end of each 4-week intervention period. Protocol compliance is monitored during both investigational and placebo intervention periods by recording the amount of formulation consumed. Formulation acceptability is assessed at the end of each intervention period by a parent questionnaire evaluating convenience, taste, and degree of acceptance of the nutritional formulation on a 10-point Likert scale or based on compliance with the study protocol and consumption of the formulation three times daily consistenty during the 4-week interventional period. Similar ranking systems to assess formulation acceptability have been used with other nutritional interventions in epilepsy populations [22–25].

Safety is assessed throughout the entire protocol period through (1) adverse event reporting and (2) assessment of clinical parameters collected throughout the protocol including anthropometrics, blood metabolism profile, dietary intake, seizure frequency, EEG, ERP, mobility, GI function, and sleep habits. In this population, the potential for negative effects of intervention must be closely monitored as patients are nonverbal. Additional file 4 contains details on collecting, assessing, reporting, and managing solicited and spontaneously reported adverse events.

Investigational and placebo formulations are administered with the serving size based on subject body weight. The investigational formulation provides beta-hydroxybutyrate, 2 g carbohydrate, 1 g protein, and 9 g fat, plus minerals, per 100 kcal. The placebo is matched for mineral content only. The formula is given orally as food or beverage three times per day.

Families will be encouraged to continue participation in the trial through weekly telephonic interviews. Data will be collected through three primary interfaces. Background information regarding the patient’s natural history will be collected by the clinical staff using the REDCap© survey. REDCap© is a secure web application that manages the trial database (21 CFR Part 11 and HIPAA compliant). Clinical visits will use either paper or electronic medical records. Data collected during home monitoring will be recorded using a tablet provided to the patient upon enrollment. The tablet is preloaded with the applications necessary to record all data during home monitoring. All data collected, regardless of patient completion status, will be shared with patients upon conclusion of the trial (last patient last visit) and assessment of the data. Additional file 4 contains details on data management and collection procedures.

### Statistical considerations

The primary outcome of the trial is to assess the tolerability of a nutritional formulation containing BHB in patients with AS. Tolerability is demonstrated through patient compliance with the protocol as determined by the amount of formulation consumed as compared to the amount prescribed and is assessed at the end of each intervention period. Premature discontinuation of the nutritional formulation by the family is also deemed as potential intolerability. Tolerability is also assessed at the end of each intervention period through a parental questionnaire. These outcome measures were chosen as this is a vulnerable, nonverbal population with limited ability to communicate and, therefore, determining if the formulation is suitable and well tolerated is an appropriate first step.

The secondary outcomes include assessment of ketosis when consuming the nutritional formulation and safety of the nutritional formulation in patients with AS. Ketosis is evaluated daily through urine testing as well as blood analysis at the end of each intervention period. The degree and timing of ketosis may be clinically relevant to demonstrating better patient nutrition as nutritional ketosis has been related to better patient outcomes as described in the background of this manuscript. Safety is evaluated by changes in motor function, cognitive function, GI tolerance, sleep, and seizures, along with changes in height, weight, and blood metabolic panels as assessed at the end of each intervention period. In addition, adverse event reporting is monitored in real time by the study coordinator.

No studies testing ketone supplementation in patients with AS exist. Therefore, sample-size estimation is based on measures of ketosis. It is assumed from murine pre-clinical investigations, non-AS clinical studies using MCT and/or BHB, and low-carbohydrate dietary interventions, that the minimal change of the secondary outcome, degree of ketosis, from the baseline to the end of the fourth week of the investigational formulation intervention period will be 100% change from baseline (baseline for standard diet is typically < 0.5mmol/L of d-BHB in blood, or < 5 mg/dL acetoacetate in urine). The acetoacetate test used is Ketostix (Bayer Corp. Diagnostics Division, Tarrytown, NY, USA) which exhibits a sensitivity of 78% and a specificity of 96% when compared to a serum standard of 14.4 ml/dL. Considering a 25% drop-out rate, an estimate of 25 subjects need to be screened to achieve 15 completers.

Descriptive statistics, such as mean and standard deviation, are used to describe continuous variables, and frequency for the categorical variables. Means are compared using a paired two-sample *t* test. Statistical significance for all tests is *p* < 0.05. Multiple comparisons can be made including: (1) each subject to serve as their own control, comparing investigational formulation to placebo formulation, as well as to baseline, (2) each dietary background group considered in aggregate, comparing investigational formulation to placebo formulation, as well as to baseline, and (3) all subjects considered in aggregate, comparing investigational formulation to placebo formulation, as well as to baseline.

Any patient who receives the study formulation for any amount of time will be included in the intent-to-treat population for study analyses. Missing data points in this population will be addressed in discussion of any published results. Data from protocol-compliant participants is the defined population for efficacy subset analyses; any participant who received both protocol-required formulations and all required clinical assessments is considered protocol compliant. Such an efficacy subset analysis will be the primary approach for determining whether the trial endpoints are met. Those patients who complete the baseline visit, but do not start Intervention Period 1 and are withdrawn from the study, will be used for natural history reportable data only but will not be included in analyses for determining whether the outcome measures of the trial have been met.

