The animal evidence supporting ketone supplementation and the clinical evidence for KDs in models of AS and seizure control, respectively, suggest that dietary interventions including exogenous ketones may be an important development in clinical management strategies. The current study is designed as an initial evaluation of ketogenic formulations used with a variety of dietary backgrounds. It represents a unique opportunity to study the potential benefits of nutritional intervention in a pediatric population (ages 4–11 years) with AS. The knowledge gained from the study may guide further evaluations in the use of exogenous ketones for nutritional strategies in the dietary management of patients AS.

It is known in the AS population that there is a large placebo effect. Our study also offers a unique design in which the use of objective measures is prioritized. We hope that this will yield measures that benefit future trials in the Angelman community in addition to a clearer understanding of the overall effectiveness and mechanism of action of BHB for inducing ketosis. The ultimate goal will be to positively impact nutritional status, which should enhance the ability of the patient to overcome the symptoms of AS such as seizures, cognition and learning, gait/mobility, and/or sleep disturbances.

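### The functional safety measures are tested only as differences in means, in the protocol-compliant subset, so worsening in individual children can be offset or dropped from the deciding analysis

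*Protocol article*

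**What the plan says.** Safety is a secondary outcome. Under Statistical considerations its functional part reads "Safety is evaluated by changes in motor function, cognitive function, GI tolerance, sleep, and seizures", and the sentence continues "along with changes in height, weight, and blood metabolic panels as assessed at the end of each intervention period". The next sentence adds a further channel: "In addition, adverse event reporting is monitored in real time by the study coordinator".

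Procedures and interventions describes two components: "Safety is assessed throughout the entire protocol period through (1) adverse event reporting and (2) assessment of clinical parameters collected throughout the protocol". It gives the reason for vigilance, "the potential for negative effects of intervention must be closely monitored as patients are nonverbal", and refers the reader elsewhere for detail: "Additional file 4 contains details on collecting, assessing, reporting, and managing solicited and spontaneously reported adverse events". That file is not among the documents available.

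The analysis text under Statistical considerations applies to all measures alike. Continuous variables are summarised by mean and SD, and categorical ones by frequency. The one test is given as "Means are compared using a paired two-sample" *t* test, with significance at p < 0.05. Comparisons of active with placebo and with baseline are listed for each subject as own control, for each diet group, and for all subjects together.

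Two populations are defined. The intent-to-treat population takes in anyone who received the study formulation for any length of time. The protocol-compliant subset requires both formulations and all required assessments, and it is the primary approach for judging whether the endpoints are met.

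The Discussion says that better nutritional status should "enhance the ability of the patient to overcome the symptoms of AS such as seizures, cognition and learning, gait/mobility, and/or sleep disturbances".

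**The concern.** The stated safety aim is to detect harm in children who cannot report it. A comparison of means asks whether the group shifted on average. Seizures, cognition, mobility and sleep appear both as safety measures and as hoped-for benefits, and GI tolerance is the only functional safety domain missing from the benefit list. If the product helps some children and harms others, the two offset each other in the mean.

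The choice of population adds to this. A child who deteriorates and stops has not completed both formulations and all assessments, so is not protocol compliant. That child drops out of the analysis that decides the endpoint, although this is the child a safety analysis most needs.

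At stake is the secondary safety conclusion of what the article presents as the first evaluation of this ingredient in such a population. The functional comparison could look neutral or favourable while a noticeable minority of children did worse on active product.

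**Working it through.** The article gives no safety figure to reproduce. The only inputs taken from it are n = 15 completers, the paired t test and the 0.05 level. Two-sided testing and all effect sizes below are assumptions for illustration.

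**1. Cancellation in one data set.** Take the change in seizure count, active against placebo, in 15 children: 12 at -30% and 3 at +100%.

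- Mean = (12 × -0.30 + 3 × 1.00)/15 = -0.60/15 = -0.04.
- SD = √[(12 × 0.26² + 3 × 1.04²)/14] = √(4.056/14) = 0.538.
- t = -0.04/(0.538/√15) = -0.29 on 14 df, p = 0.78.
- Counted per child: 3/15 = 20% worsened, Clopper-Pearson 95% interval 4% to 48%.

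**2. Effect of dropping children who stop.** In the same data, suppose some of the three who worsened stop and leave the compliant subset.

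- One leaves: (-3.60 + 2.00)/14 = -11%.
- Two leave: (-3.60 + 1.00)/13 = -20%.
- All three leave: -3.60/12 = -30%.

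The deciding mean becomes more favourable with each child who worsens and stops.

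**3. Behaviour over repeated trials.** Simulation with n = 15, residual SD 1 and 40,000 trials per scenario. Positive means better.

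| Assumed mix | True mean | P(significant worsening) | P(mean favourable) |
|---|---|---|---|
| 3 worse by 2 SD, 12 unchanged | -0.4 | 0.14 | 0.06 |
| 3 worse by 2 SD, 12 better by 0.5 SD | 0 | 0.003 | 0.50 |
| 5 worse by 2 SD, 10 better by 1 SD | 0 | < 0.001 | 0.50 |
| 3 worse by 2 SD, 12 better by 1 SD | +0.4 | < 0.001 | 0.94 |

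Even with no child improving, the test flags clear harm in one child in five only 14% of the time.

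**4. What a count can and cannot show.** If a defined worsening has a true rate of 5%, 10% or 20%, at least one case among 15 is seen with probability 1 - (1 - rate)^15 = 0.54, 0.79 or 0.96. If none is seen, the one-sided 95% upper limit is 1 - 0.05^(1/15) = 0.18.

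A count in one direction only is noisy. Assume no product effect and Poisson seizure counts averaging 4 per period. The active count is then at least double the placebo count by chance in about 22% of children, so 3 or more of 15 appear worse in about 68% of trials, from 1 - P(X ≤ 2) with X binomial(15, 0.22). At averages of 8 and 16 per period the chance per child falls to about 11% and 4%. The count in the opposite direction is therefore needed as a comparator.

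**The case against.** A reader might infer that safety as a whole is defined as mean change. It is not. The safety sentence speaks of changes, and the mean comes from the general methods text. Adverse event reporting is the first safety component. Growth and blood measures are included, families are interviewed by telephone weekly, seizures, sleep and GI health are followed at home, and a Data Safety Monitoring Board with a biostatistician meets three to four times a year. Worsening could be seen through any of these. Whether gradual deterioration would escape adverse event reporting cannot be judged without Additional file 4. All of this stands, and it limits the point to the functional comparison.

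A reader might also infer that a non-significant test will be read as proof of safety. No such rule is written, the study is called exploratory, and an SD of 54% beside a mean of -4% would itself signal spread. Nor can diet pooling be blamed outright, since per-diet comparisons are listed. The own-control comparison supplies the contrast needed, but with no direction or degree of worsening attached.

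The benefit statement is an ultimate goal in the Discussion, not an endpoint. That weakens the wording of the overlap but not the arithmetic, which needs only that some children improve, for whatever reason.

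Finally, margins and displays commonly belong in an analysis plan, and their absence here is not the criticism. The criticism is of what is stated: the one test and the deciding population do not fit the stated safety aim, and a plan that follows this text would inherit both. The compliant subset is labelled an efficacy analysis, but the text applies it to the trial endpoints without exempting safety.

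**Conclusion.** The point holds for the functional safety measures. With a t test on means as the only named test and the protocol-compliant subset as the deciding population, worsening in 20% to 33% of children can coexist with a neutral or favourable result, and children who worsen and stop move that result further in the favourable direction.

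The sizes rest on assumed effects, 15 children and two-sided testing. They describe the comparison of means and not the adverse event data. The documents do not support the stronger conclusions that the trial has no means of noticing harm in an individual child, or that it will declare safety from a non-significant test. The change is worth making before unblinding.

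**What to change.** - Analyse safety in every child who received any formulation, not in the protocol-compliant subset. A child with data from only one period has no active-placebo pair. Show that child against baseline and list the child separately.
- Keep the means and the adverse event report. Beside them, give for each functional domain a paired display of each child's active and placebo values.
- For each domain, report the number of children worse on active than on placebo beyond a margin fixed before unblinding, and the number worse on placebo than on active by the same margin, each with an exact interval. The second count shows how much of the first could be chance.
- State that no conclusion of safety will be drawn from a non-significant mean difference.

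The data are already to be collected, so the cost is analysis wording and agreeing a margin per domain in advance. The limitation is precision: with about 15 children the intervals will be wide, and even 0/15 leaves a rate of up to 18% possible (one-sided 95%).
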